
**Figure 4 fig4:**
[figure not shown]
Examples of sEMG and MSK US inspection operations. **(A)** Examples of sEMG inspection operations. **(B)** Examples of MSK US inspection operations.

The VAS is assessed prior to the first treatment and after each subsequent treatment session. Medication usage was evaluated before the initial treatment and after the second, third, and fourth weeks of treatment. The ODI, SF-36, BDI-II, BAI, sEMG, and MSK US assessments were performed for patients with chronic nonspecific low back pain prior to the first treatment and upon completion of the treatment phase. Additionally, follow-up evaluations were conducted at 4, 8, and 12 weeks after the conclusion of the treatment intervention, primarily collecting data on patients’ pain VAS, ODI, and medication usage during clinical visits (see Table 2).

**Table 2 tab2:** The schedule of enrollment, interventions, and assessment.

Visit item	Enrollment	Allocation	Treatment period					Follow-up period		
Time point	−3–0 day	0 day	1 day	1 week	2 week	3 week	4 week	8 week	12 week	16 Week
Register	✓									
Sign the informed consent form		✓								
General information		✓								
Inclusion and exclusion criteria		✓								
Randomization		✓								
Basic information, current medical history, past medical history		✓								
Intervation										
Tuina combined with Loxoprofen Sodium patches										
Loxoprofen Sodium patches										
Assessments										
VAS		✓	✓	✓	✓	✓	√	√	√	√
ODI		✓					√	√	√	√
SF-36		✓					√			
sEMG		✓					√			
BDI-II		✓					√			
BAI		✓					√			
MSK-US		✓					√			
Medication usage		✓		✓	✓	✓	√	√	√	√
Safety evaluation										
Adverse events										

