### Blinding

Due to the specific nature of the manipulative intervention, blinding of participants and practitioners was not feasible. Therefore, this study implements blinding only for the objective outcome assessments and statistical analysis. Specifically, the assessors of sEMG and MSK US, as well as the data analysts, are unaware of group assignments and treatment details. However, patient-reported outcome measures, including VAS, ODI, SF-36, BDI-II, and BAI, are self-reported by participants who are aware of their treatment allocation; thus, these subjective outcomes remain at risk of detection bias. A three-separation principle—separating clinical intervention, objective outcome evaluation, and data analysis—was implemented to minimize bias where feasible. To protect the blind, objective assessors are instructed to avoid discussing treatment-related details with participants, and participants are reminded not to reveal their group assignment during assessments.

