#### Experimental group

The experimental group received Tuina combined with the Loxoprofen Sodium patch. The Tuina intervention will be performed by a physician with over 10 years of experience in Tuina treatment from the Department of Tuina, the Affiliated Rehabilitation Hospital of Fujian University of Traditional Chinese Medicine. The patient is first guided to assume a prone position. The Tuina therapist sequentially applies the rolling manipulation and palmar pressing-kneading manipulation to the Bladder Meridian on both sides of the lower back and the posterolateral aspect of the affected lower limb. Each region is treated for 5 min, totaling 10 min, to alleviate muscle tension. Maintaining the same position, finger-pressing manipulation is applied to the acupoints of Ashi, BL23 (Shenshu), GV4 (Mingmen), BL25 (Dachangshu), BL26 (Guanyuanshu), BL54 (Zhibian), GB30 (Huantiao), BL40 (Weizhong): (see Figure 2 and Table 1), with force generated from the forearm and fingers. The intensity is adjusted to the patient’s comfort level, and rhythmic pressing and kneading are performed for 5 min. The patient is then guided to a lateral recumbent position. The Tuina therapist first applies thumb-plucking manipulation to the bilateral erector spine muscles for 3 to 5 repetitions, followed by lumbar oblique-pulling manipulation once on each side, until the audible sound of bubbles (“click” sound) in the joint cavity can be heard at the end of the operation. Subsequently, the patient returns to the prone position, and the bilateral sacrospinal muscles are patted, followed by tapping on the lumbosacral region to relieve spasm, alleviate pain, and relax the sinews and unblock the meridians. The intervention is administered three times weekly, with each session lasting 30 min, for a continuous treatment duration of 4 weeks.

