#### Control group

During the 4-week treatment period, the control group received the Loxoprofen Sodium Patch [Specification: 50 mg/patch, Manufacturer: Daiichi Sankyo (China) Investment Co., Ltd., China Drug Approval Number: H20040130] was applied as needed (pro re nata) once daily to the painful area of the lower back on days when pain intensity became bothersome or exceeded a tolerable baseline, and avoiding application to any area with bruising or abrasions. It was applied to the painful area of the lower back once daily upon the onset of pain and discontinued upon pain relief. Participants were also required to complete a medication record form.

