#### Primary outcome

Primary Outcome: The primary outcome measure of this trial is the change in pain intensity from baseline to the end of the 4-week treatment period, assessed via a VAS (21). The VAS is a sensitive, continuous, and reliable instrument for quantifying subjective pain perception. A standard 100-mm VAS will be employed, anchored by the verbal descriptors “0 mm = no pain” at the left end and “100 mm = the worst pain imaginable” at the right end. To account for the fluctuating nature of chronic low back pain, patients will be instructed to use the VAS to rate their average pain intensity over the past week. A higher measurement (in millimeters) indicates greater pain severity.

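### VAS ratings are tied to treatment sessions that only the Tuina arm has, in conflict with Table 2, so the week-4 primary rating may be taken under different conditions in the two arms

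*Protocol article*

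**What the plan says.** The Primary outcome section defines the endpoint as "the change in pain intensity from baseline to the end of the 4-week treatment period, assessed via a VAS". It adds that "patients will be instructed to use the VAS to rate their average pain intensity over the past week".

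The timing of the VAS is then given twice under Secondary outcomes. The paragraph just above Table 2 says that "The VAS is assessed prior to the first treatment and after each subsequent treatment session". Table 2 ("The schedule of enrollment, interventions, and assessment") has one VAS row for the whole trial, marked at day 0, day 1 and weeks 1, 2, 3, 4, 8, 12 and 16.

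On treatment, the Experimental group section says: "The intervention is administered three times weekly, with each session lasting 30 min, for a continuous treatment duration of 4 weeks". The Control group section describes only an as-needed patch and a medication record form: "It was applied to the painful area of the lower back once daily upon the onset of pain and discontinued upon pain relief". It mentions no treatment session.

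The Blinding section states that the VAS and the other questionnaires "are self-reported by participants who are aware of their treatment allocation".

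**The concern.** The timing rule for the sole primary outcome rests on an event that exists in one arm only, and it disagrees with the table it introduces. Both cannot be followed. Nothing fixes the week-4 rating at the same point relative to treatment in the two arms, and the only sentence on the order of rating and session says the rating comes after.

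A participant who knows the allocation and has just had hands-on treatment may let current relief, current soreness or the treatment setting colour a recalled average. A control participant rates without that experience. Any difference this produces goes straight into the between-arm comparison, and randomisation does not remove it. The Discussion already concedes that there is no attention-matched control and that assessor blinding does not protect the VAS. Unequal timing would add a further difference, and unlike those it is easy to avoid.

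**Working it through.** **1. The two schedules side by side**

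- Sessions in the Tuina arm: 3 per week × 4 weeks = 12.
- Text rule, Tuina arm: one rating before session 1 and one after each of the 12 − 1 = 11 later sessions.
- Text rule, control arm: at most a baseline rating, because no session follows.
- Table 2, both arms: day 0, then five treatment-period points (day 1, weeks 1, 2, 3, 4), then weeks 8, 12 and 16.

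Table 2 gives controls a week-4 rating. It does not say whether the Tuina week-4 rating comes before or after that day's session, or how long after the last one.

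**2. Fit with the 7-day recall**

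- Three ratings a week are on average 7/3 = 2.3 days apart, so successive 7-day windows share about 7 − 2.3 = 4.7 days.
- A day-1 rating covers about 6 pre-treatment days out of 7.
- In a true 7-day average, relief lasting h hours after the final session counts for only h/168 of its size (7 × 24 = 168). This limits a purely momentary effect, unless current pain colours the recall.

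**3. The plan's own figure**

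Inputs from Sample size: week-4 VAS 26.2 ± 13.7 and 36.4 ± 14.8 mm, two-sided α = 0.05, power 80%, dropout 20%.

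- Difference: 36.4 − 26.2 = 10.2 mm.
- Pooled SD: √((13.7² + 14.8²)/2) = √203.365 = 14.26 mm.
- d = 10.2/14.26 = 0.715. A two-sample t-test (noncentral t) needs 32 per group, and 32/0.8 = 40.

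The stated 32 and 40 reproduce. The stated d of 0.804 does not follow from these inputs. That is a separate matter and does not affect this point.

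**4. Size of the risk**

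Let b be a shift in the Tuina arm's recalled week-4 average caused only by timing. The documents give no value, so b is an assumption. With no lasting difference, the test statistic has noncentrality (b/14.26) × √(n/2) on 2n − 2 degrees of freedom.

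| Assumed b (mm) | Share of 10.2 mm | Noncentrality, n = 40 | P(p < 0.05), 40 per arm | P(p < 0.05), 32 per arm |
|---|---|---|---|---|
| 1 | 10% | 0.31 | 6.1% | 5.9% |
| 2 | 20% | 0.63 | 9.5% | 8.6% |
| 3 | 29% | 0.94 | 15.3% | 13.2% |
| 5 | 49% | 1.57 | 34.1% | 28.2% |

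For power, replace b by 10.2 − b at 32 per arm. For b = 1, 2, 3 or 5 mm, power is 72%, 62%, 51% or 30%, against the planned 80%. This reads in two ways. It is the power for the lasting part if b of the planned 10.2 mm is transient. It is also the power of the trial if the true effect is 10.2 mm and post-session soreness raises Tuina ratings by b.

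**The case against.** The best defence is that the primary time point is set elsewhere for both arms. The Primary outcome section, the Abstract and the Sample size section all refer to the end of the 4 weeks, and Table 2 marks week 4 without splitting by arm. The session sentence can be read as loose wording about monitoring during treatment. The recall period was also chosen to smooth fluctuation, which works against a momentary effect. Part of the problem, unblinded self-report, is already disclosed and would remain after any rescheduling.

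Much of this stands, and it rules out several stronger readings that a reader might infer:

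- **That the week-4 VAS is read immediately after the last session.** The text says only that it comes after, with no interval, and nothing puts the week-4 visit on a session day.
- **That controls have no primary assessment.** Table 2 gives them one.
- **That the bias favours Tuina.** The Adverse events section lists worsening local pain and transient muscle soreness among the common events after Tuina, so the sign is not settled.
- **That per-session ratings distort the mixed model.** The Statistical analysis section does not say they enter it, and the choice of visits can be left to an analysis plan. Unequal numbers of records are not in themselves a bias in such a model.

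What the defence does not remove is the contradiction. The written rule differs from Table 2, cannot be applied in one arm, and leaves the timing of the primary rating relative to treatment open in the other.

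**Conclusion.** The point holds as an internal conflict that creates a risk of non-comparable timing for the primary outcome. The documents do not show that a transient effect enters the comparison, how large it would be, or in which direction.

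The percentages rest on four assumptions: the pilot SDs, an unadjusted t-test at week 4, no lasting difference, and a timing shift b in the recalled average that is assumed throughout. Because the recall covers a week, the low end is more plausible. At 1 to 2 mm the false-positive rate with 40 per arm would be 6.1% to 9.5%. The 15.3% and 34.1% at 3 and 5 mm show the sensitivity and are not forecasts.

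It is worth correcting now. The Trial status section reports 9 participants enrolled at submission and recruitment until June 30, 2027, so most primary ratings can still be taken under one rule. A difference in timing cannot be repaired at analysis.

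**What to change.** 1. Replace the session-based sentence with the Table 2 schedule, and state that it applies identically to both arms.
2. Take the week-4 VAS in both arms in the same window after randomisation, on a non-session day or before any session that day.
3. Base the efficacy analysis, including the mixed model, on the post-baseline visits common to both arms: weeks 1, 2, 3, 4, 8, 12 and 16. Leave the day-1 rating out of efficacy, since it recalls almost only pre-treatment days.
4. If per-session ratings are kept, report them descriptively only, because their 7-day windows overlap.
5. For participants already enrolled, record when the VAS was taken relative to the last session.

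The cost is protocol wording and visit scheduling. Some Tuina participants may need a week-4 assessment on a separate day or shortly before a session, which is a small inconvenience. The sample size and the treatment schedule do not change.

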### Adverse events

In this study, the monitoring, assessment, and management of adverse events related to Tuina followed a comprehensive standard operating procedure. Initially, any discomfort reported during the intervention period was promptly evaluated and judged by at least two clinical experts with senior professional titles from our research group. According to previous literature and clinical consensus, common adverse events associated with Tuina manipulation primarily include worsening local pain or discomfort, skin redness or ecchymosis, transient muscle soreness, and, in rare instances, temporary dizziness or fatigue; the adverse reactions associated with Loxoprofen Sodium patches, including gastrointestinal discomfort, contact dermatitis, and erythema at the application site. Upon confirmation of any adverse event, a detailed record was made, and the event was reported to the study’s ethics committee within 24 h.

Management was implemented based on the severity of the event using a graded approach: For mild local discomfort, participants could continue in the study under close observation. For moderate pain exacerbation or persistent dizziness, the current treatment cycle was immediately suspended, and symptomatic treatment was provided until complete symptom resolution and safety were confirmed through evaluation. In the event of a serious adverse event, the research intervention for that subject was immediately and permanently terminated, emergency procedures were initiated, and reports were submitted to the relevant authorities within the mandated timeframe. Furthermore, if prohibited concomitant treatments, such as the systemic use of other analgesic medications or receiving other physical therapies, were used to manage an adverse event, or if the event led to the subject being unable to complete follow-up for primary outcome measures, including pain scores, functional disability indices, and surface electromyography assessments, the data from lost-to-follow-up participants will be supplemented using multiple imputation and included in the final efficacy analysis. Their safety data were retained and reported.

### Patient and public involvement

In this study protocol, participants and the general public will not be involved in all stages of the study. The role of participants will be confined to those aspects directly relevant to the core objectives of the research, and they will not be engaged in the recruitment, implementation, or reporting phases of the study. Their search findings will be disseminated to participants and the public through educational lectures, brochures, or pamphlets. Moreover, the results will be published in open-access, peer-reviewed journals.

### Data management

Each enrolled subject was required to have a completed Case Report Form (CRF). Dedicated assessment personnel entered data into the CRF completely, truthfully, and accurately. After verification and signature by the clinical research monitor, the CRF was promptly transferred to the data administrator, who then accurately entered the CRF data into the database. This database automatically validates the input data and flags any inconsistent or questionable data, after which the data administrator sends a query request to the researchers, and upon the researchers’ approval, these data are checked and corrected. All data were entered independently by two individuals in duplicate. The software automatically verified entries and flagged any inconsistent or questionable data, after which the data administrator sends a query request to the researchers, and upon the researchers’ approval, these data are checked and corrected. A random 10% of the CRFs were subjected to manual verification. After all data were confirmed to be accurate, the database was locked by the principal investigator, statistician, and the person responsible for blinding. No further modifications were permitted to the locked data files. Regarding data preservation, investigators were required to retained for a minimum of 5 years after the completion of the trial all study materials, including all original source data such as imaging discs, data files, CRFs, and informed consent forms.

### Sample size

Based on the study design, the VAS score after the 4-week treatment was designated as the primary outcome measure. According to the data from preliminary pilot studies, after 4 weeks of intervention, the VAS score of 26.2 ± 13.7 mm for the experimental group and 36.4 ± 14.8 mm for the control group. Using G*Power 3.1^1^ software to estimate the sample size, a two-independent-sample *t*-test was selected for estimation. Setting *α* = 0.05, *β* = 0.2, and using a two-sided statistical test, the calculated effect size d was 0.804, based on which it was estimated that 32 participants are needed per group. Considering a potential dropout rate of 20%, the final sample size was determined to be 40 participants per group, totaling 80 participants.

### Statistical analysis

Statistical analysis will follow the ITT principle, including all randomly assigned participants. Data from all lost-to-follow-up participants will be completed using multiple imputation, and statistical analysis will be conducted using SPSS 26.0 software. All continuous variables will be first tested for normality. Normally distributed data were presented as mean ± SD, and t-tests were performed for statistical analysis; while non-normally distributed data will be presented as M (P25, P75), and statistical analysis was performed using the Mann–Whitney U test. Categorical variables will be expressed as frequencies or percentages, and statistical analysis was performed using the chi-square test. The longitudinal analysis will be performed using a linear mixed model with baseline value as covariate. A two-sided *p*-value of <0.05 will be considered statistically significant. To address the problem of multiple Type I errors, the Bonferroni correction method will be used to adjust the significance level.

For safety analysis, the number of cases with abnormal changes in laboratory indicators will be described, and the incidence, presentation, severity, and correlation with the intervention will be reported in detail for all adverse events.

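### Outcomes that fail the normality test are multiply imputed and then compared by Mann-Whitney U, which leaves several p-values and no defined single result

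*Protocol article*

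**What the plan says.** The Statistical analysis section sets out this sequence:

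- Missing data: "Data from all lost-to-follow-up participants will be completed using multiple imputation, and statistical analysis will be conducted using SPSS 26.0 software". The Adverse events section repeats that "the data from lost-to-follow-up participants will be supplemented using multiple imputation and included in the final efficacy analysis".
- Choice of test: "All continuous variables will be first tested for normality".
- If normal: "Normally distributed data were presented as mean ± SD, and t-tests were performed for statistical analysis".
- If not normal: "non-normally distributed data will be presented as M (P25, P75), and statistical analysis was performed using the Mann–Whitney U test".
- Repeated measurements: "The longitudinal analysis will be performed using a linear mixed model with baseline value as covariate".

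The Secondary outcomes text and Table 2 place SF-36, BDI-II, BAI, sEMG and MSK US at baseline and at week 4 only. VAS, ODI and medication usage are measured repeatedly up to week 16. The Sample size section plans for 20% dropout, with 40 participants per group.

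**The concern.** Multiple imputation gives several completed datasets, and the usual way to reach one answer is to take an estimate and its standard error from each and combine them. The t-test and the mixed model supply both. The Mann-Whitney test, reported with medians and quartiles, supplies neither.

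An outcome with one post-baseline value has no clear place in a longitudinal model. If it is skewed, the Mann-Whitney test is the only between-group comparison the article gives it. sEMG and MSK US are in this group, and the Blinding section makes them the only outcomes with blinded assessors.

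The normality test adds a second ambiguity. If it is run on each completed dataset, its verdict can change from one to the next, and the planned test changes with it. The analyst would then have to choose a way to reduce several p-values to one with the results in view.

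**Working it through.** **Inputs from the protocol article (Sample size).** VAS 26.2 ± 13.7 against 36.4 ± 14.8 mm, two-sided alpha 0.05, power 80%, 20% dropout, 40 per group.

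**The plan's own figure.** Pooled SD = √((13.7² + 14.8²)/2) = √203.4 = 14.26. The difference is 36.4 − 26.2 = 10.2, so d = 10.2/14.26 = 0.715. The two-sample t-test then needs 31.7, so 32 per group, and 32/0.8 = 40. The stated sample size is reproduced from the means and SDs. (The printed d of 0.804 does not follow from them; that is a separate point.) At the planned dropout, 40 × 0.2 = 8 values per group are imputed.

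**What pooling needs.** With estimates Qᵢ and variances Uᵢ from m datasets, Rubin's rules give Q̄ = mean(Qᵢ) and T = mean(Uᵢ) + (1 + 1/m)·B, where B is the variance of the Qᵢ. A U statistic with its p-value, or a median with quartiles, provides no pair (Qᵢ, Uᵢ).

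**Simulation assumptions (not in the article).** Baseline correlation 0.5; imputation from a normal model with arm and baseline; 5 or 20 imputations; Mann-Whitney in each completed dataset. Set A has 3,000 trials per setting, with gamma or normal outcomes at the VAS mean and SD, or a skewed score with mean 10 and SD 8. Set B has 400 trials per setting, with a gamma outcome of shape 2 and SD 14.26. Monte Carlo error near 20% is about √(0.2 × 0.8/400) = 2 points in set B and 0.7 points in set A.

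**Trials in which the p-values of one trial fall on both sides of 0.05**

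| Setting | Set A, m = 5 | Set B, m = 5 | Set B, m = 20 |
|---|---|---|---|
| No effect, 20% missing | 16–17% | 18% | 29% |
| 10.2 mm, 20% missing | 22–24% | 20% | 27% |
| 7 mm, 20% missing | not run | 38% | 55% |
| 10.2 mm, 5% missing | not run | 5% | 8% |

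For set A's skewed score with an assumed difference of 4 points, the figure was 32%.

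**Normality verdict.** With 20% missing and Shapiro-Wilk run in every completed dataset, the verdict differed between imputations of the same trial in 14–46% of trials (set A) and 24–47% (set B).

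**Type I error of the shortcuts (20% missing, m = 5).**

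- Median p: 7–8%.
- Significant if any p < 0.05: 19–20%.
- Stacking the five datasets: 42–43%.
- Baseline-adjusted linear model pooled by Rubin's rules, for comparison: 5.4%.

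**Hand check on stacking.** Stacking treats 5 × 40 = 200 values per group as independent, so the nominal variance of a group mean is proportional to 1/200 = 0.005. With 32 observed, 40 baselines and correlation 0.5 (squared, 0.25), the true variance is about 0.75/32 + 0.25/40 = 0.0297. The ratio is 5.94 and its root 2.44. The effective critical value is 1.96/2.44 = 0.80, which has a two-sided tail of about 0.42. This agrees with the simulation.

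**A single rank-based result is obtainable.** In one simulated skewed dataset (20% missing, m = 20), the Mann-Whitney p-values ran from 0.000006 to 0.0026. Pooling the probability index with its standard error gave 0.7466 (SE 0.0621), so z = (0.7466 − 0.5)/0.0621 = 3.97 and p = 0.00007.

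**The case against.** The strongest reply is that only one sentence is missing. Number of imputations, imputation model and combining rule are normal content for a statistical analysis plan, and that plan is not shown. P-values also vary between imputations under any test. Even at the design difference with 20% missing, all p-values were on the same side of 0.05 in 73–80% of simulated trials.

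Much of this stands. The absence of imputation details is not part of this point. What remains is that the article fixes a test whose usual output does not pool, so an analysis plan would have to replace or supplement that test. Variation between imputations does no harm when the combining rule absorbs it, as it does for a t-test or the mixed model. Here no rule does.

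A reader might infer more than the article supports:

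- **That imputation and a rank test cannot be joined.** They can, through the probability index, as shown above.
- **That every outcome is affected.** Outcomes judged normal get a t-test, and repeated outcomes have the mixed model; both pool.
- **That the chi-square test raises the same problem.** The article lists no categorical efficacy outcome, so this has little to act on.
- **That normality verdicts will conflict.** The article does not say the test is run in each completed dataset. Running it once on observed data would avoid this.
- **That imputed scores will fall outside their range.** This depends on the imputation model, and the article names none.

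**Conclusion.** The point holds in a limited form. For an outcome with missing data that is judged non-normal and compared by the two-group test, the plan as written yields several p-values and no defined single result. This concerns mainly SF-36, BDI-II, BAI, sEMG and MSK US. The primary VAS is exposed only if it fails the normality test and the two-group comparison is used; its sample size was based on a t-test.

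The size depends on assumptions about skewness, baseline correlation, number of imputations and how much is missing. At the planned 20% dropout the p-values straddle 0.05 in about 16–29% of trials, under no effect and at 10.2 mm; with less dropout it is fewer. The type I error figures of about 7–8%, 20% and 42% belong to shortcuts that the article neither names nor excludes. They show what improvisation could cost and do not predict what the analysts will do.

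**What to change.** For every continuous efficacy outcome, whatever the normality test shows, fit a baseline-adjusted linear model in each imputed dataset, with a robust or bootstrap standard error if the outcome is skewed. Pool the group difference by Rubin's rules and report it with its confidence interval. Keep medians, quartiles and rank tests as descriptive or sensitivity analyses. If a rank-based result is wanted, name a statistic that can be pooled, such as the probability index with its standard error.

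The cost is a few sentences in the analysis section and a little programming, with no new data. The downside is that rank tests are no longer the main test for skewed outcomes. Trial status reports 9 participants enrolled, no interim analysis and an unlocked database, so the change can still be made before any outcome data are analysed.

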**Study design and methods:**

This is a single-center, randomized controlled, assessor-blind clinical trial. A total of 80 participants aged 18–60 years meeting the diagnostic criteria for CNLBP will be recruited and randomly assigned to either the experimental group (Tuina combined with Loxoprofen Sodium patches) or the control group (Loxoprofen Sodium patches). The Tuina intervention will be administered three times weekly for four consecutive weeks; Loxoprofen Sodium patches will be used as needed. The primary outcome measure is the Visual Analogue Scale (VAS) for pain after 4 weeks of treatment. Secondary outcomes include the Oswestry Disability Index (ODI), 36-Item Short Form Health Survey (SF-36), Beck Depression Inventory-Second Edition (BDI-II), Beck Anxiety Inventory (BAI), Surface Electromyography (sEMG) and musculoskeletal ultrasound (MSK US) parameters, medication usage, and 12-week follow-up data. Statistical analysis will follow the intention-to-treat (ITT) principle, using SPSS 26.0 for between-group comparisons and repeated measures analysis.

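### The primary endpoint is a change score in one section and a week-4 score in others, and the plan does not say whether a normality-gated unadjusted test or the planned baseline-adjusted model gives the primary result.

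*Protocol article*

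**What the plan says.** The endpoint is described in three places in the protocol article, and they do not agree.

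- Primary outcome section: "the change in pain intensity from baseline to the end of the 4-week treatment period".
- Abstract, study design and methods: "The primary outcome measure is the Visual Analogue Scale (VAS) for pain after 4 weeks of treatment".
- Sample size section: "the VAS score after the 4-week treatment was designated as the primary outcome measure". The calculation rests on pilot week-4 values, "the VAS score of 26.2 ± 13.7 mm for the experimental group and 36.4 ± 14.8 mm for the control group", and "a two-independent-sample *t*-test was selected for estimation".

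The Statistical analysis section gives a general rule for all continuous variables: a normality test comes first, then "Normally distributed data were presented as mean ± SD, and t-tests were performed for statistical analysis", with a Mann-Whitney U test for non-normal data. It then adds: "The longitudinal analysis will be performed using a linear mixed model with baseline value as covariate". Data of participants lost to follow-up are to be multiply imputed. No sentence assigns the t-test, the Mann-Whitney test or the mixed model to the primary endpoint.

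**The concern.** A week-4 score and a change from baseline are different variables with different SDs. Under an unadjusted test they give different estimates, p-values and power, and only the week-4 score was used to size the trial.

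The normality rule adds a second ambiguity. It makes the test depend on the observed data, and with it the hypothesis: a difference in means on one branch, a rank comparison on the other. It also fits poorly with multiple imputation. Standard pooling combines an estimate and a standard error from each imputed dataset, and a Mann-Whitney p-value supplies neither directly. Different imputed datasets could also fall on different sides of the gate, and no rule covers that.

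Two variables crossed with two tests, plus the mixed model, make five readings of the primary analysis. The one that uses baseline best is already planned but has no stated role for the primary result. At stake are a single prespecified primary p-value and some precision that could be had at no cost.

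**Working it through.** **Inputs from the Sample size section.** Week-4 means 26.2 and 36.4 mm, SDs 13.7 and 14.8 mm, 32 per group before dropout, and "Setting *α* = 0.05, *β* = 0.2, and using a two-sided statistical test".

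**Reproducing the plan's figure.**
- Difference = 36.4 − 26.2 = 10.2 mm.
- Pooled SD = √((13.7² + 14.8²)/2) = 14.26 mm.
- d = 10.2/14.26 = 0.715.
- The two-sample t-test (noncentral t) needs 32 per group; power at 32 is 80.4%.
- With 20% dropout: 32/0.8 = 40 per group, 80 in total.

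The sample size reproduces. The stated d of 0.804 does not: it would need only 26 per group. It coincides with the achieved power of 0.804. This is a separate slip and does not alter the sample size.

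**Power of the three mean-based analyses at 32 per group.** The baseline/week-4 correlation r is not in the document, so a range is assumed.
- Unadjusted week-4 score: SD = 14.26, whatever r is.
- Baseline-adjusted: SD = 14.26 × √(1 − r²).
- Unadjusted change score, assuming baseline SD equals week-4 SD: SD = 14.26 × √(2(1 − r)).

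| r (assumed) | Week-4 score | Baseline-adjusted: SD, power | Change score: SD, power |
|---|---|---|---|
| 0.3 | 80% | 13.60, 84% | 16.87, 66% |
| 0.5 | 80% | 12.35, 90% | 14.26, 80% |
| 0.6 | 80% | 11.41, 94% | 12.76, 88% |

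**How far the change-score column depends on the baseline SD.** In general, Var(change) = SD_w4² + SD_b² − 2·r·SD_b·SD_w4. This equals SD_w4² when r = SD_b/(2 × SD_w4), which is the break-even against the week-4 score. No baseline SD is given, so three values are assumed.

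| Baseline SD (assumed) | Break-even r | Change-score power at r = 0.3 |
|---|---|---|
| 14.26 mm | 0.50 | 66% |
| 10 mm | 10/28.52 = 0.35 | 78% |
| 8 mm | 8/28.52 = 0.28 | 81% |

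**Why adjustment also settles the definition.** Let g be group, b baseline and y the week-4 score. The model y − b = a + τg + βb is the same as y = a + τg + (β + 1)b. The treatment effect τ and its standard error are identical for score and change.

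**The case against.** The strongest reply is that the article never assigns the unadjusted test to the primary endpoint. The t-test/Mann-Whitney rule is a general sentence, VAS is measured repeatedly, and the abstract announces both between-group comparisons and repeated measures analysis. The adjusted mixed model may therefore already be the intended VAS analysis, and under that model the two endpoint wordings give the same effect. Naming the primary test is also often left to a fuller document. This stands in part: it rules out saying that the primary endpoint is to be tested without adjustment. It does not remove the conflicting definitions, nor a gate that as written covers every continuous variable, VAS included.

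Four stronger readings are tempting, and the document does not support them.

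- *The trial misses its planned power.* The week-4 t-test used for sizing delivers 80.4% under the pilot figures. Adjustment is a gain over the plan and does not repair a shortfall.
- *The entry rule of VAS at least 40 mm makes a change score worse.* Truncating baseline lowers r, but it also lowers the baseline SD and, under a linear relation, leaves the slope unchanged. Var(change) is then SD_w4² + SD_b²(1 − 2 × slope). With slope 0.3 and week-4 SD held at 14.26, power rises from 66% to 73% to 76% as baseline SD falls from 14.26 to 10 to 8 mm. The penalty shrinks.
- *The gate will often switch the test, with large effect.* Two independent 5% normality tests on normal data give at least one failure in 1 − 0.95² = 9.75% of trials by construction, and testing each arm at 5% is itself an assumption. With normal data at the pilot values, simulated power was 82% for the t-test and 79% for Mann-Whitney, with different verdicts in 5% of trials.
- *The type I error is inflated.* In simulation with no true effect, at least one of the five analyses had p < 0.05 in about 10–12% of trials. That bound assumes free choice after seeing all the results, which nothing in the document suggests. Each test alone holds about 5%.

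**Conclusion.** The concern holds as a contradiction in the endpoint definition plus a badly fixed test rule. It should be fixed, but it does not undermine the trial's sizing.

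Naming the adjusted analysis would raise power from 80% to about 84–94% at 32 per group, for assumed correlations of 0.3 to 0.6. If the change-score definition were followed with an unadjusted t-test, power could lie below or above 80%. Which it is depends on the baseline SD and the correlation, and the document gives neither. All power figures take the pilot difference and SDs at face value.

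The Trial status section reports 9 participants enrolled, no interim analysis and an unlocked database, so a clarification now would still count as prespecified.

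**What to change.** 1. Use one endpoint wording, the VAS score at week 4, in the abstract, the Primary outcome section and the Sample size section.
2. Name one primary analysis: the between-group difference in week-4 VAS with its 95% CI, from the planned linear mixed model (treatment, visit, treatment-by-visit, baseline VAS) or the equivalent ANCOVA. This estimate and its standard error pool directly across imputed datasets.
3. Remove the normality gate for the primary outcome. Keep the unadjusted t-test and a rank-based test as sensitivity analyses only.
4. While editing the Sample size section, correct the stated effect size to about 0.715; the number of participants stays the same.

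The cost is a few sentences in the endpoint and analysis sections. No extra data or patients are needed.
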